#### Phase II: external validation-comparative study

2.3.2

The goal of the second phase of the task was to comparatively confirm the diagnostic accuracy of the additional diagnostic assessment using the AI models built in the first phase to assist clinicians in diagnostic assessment. We categorised clinicians into residents, attending physicians and chief physicians according to their experience level. We asked clinicians in the control group to independently judge these influenza cases without the assistance of the AI model; while clinicians in the experimental group did the diagnostic assessment of these influenza cases with the assistance of the AI model. Under this comparison, the metrics of AUC, sensitivity, specificity, and diagnostic consumption time are what are used to initially evaluate the performance of the AI model. Imagine the exciting news that an AI model-assisted clinician can complete a diagnostic assessment with 95% accuracy in just 10 minutes. This dual assessment framework quantifies the added value of AI models in the real world.

#### Phase III: multi-reader, multi-case validation

2.3.3

Phase 3 used a two-round diagnostic design for evaluating the impact of AI model assistance on the effectiveness of clinician decision-making. The AI models used in Phase 3 were calibrated in the Phase 2 validation phase. Recruited clinicians are split into two rounds subsequently evaluating cases independently then filling in the diagnosis.

The first round of tasks that clinicians receive is the baseline diagnostic assessment. In the baseline diagnostic assessment, clinicians are required to evaluate cases using a standard influenza diagnostic protocol and subsequently complete the diagnostic results.

The second round of tasks allows clinicians to access the risk scores and key influencing factor scores generated by the AI model to fill in the diagnosis during the evaluation of the case.

All clinicians were required to undergo two rounds of tasks. This was done with reference to a previous study (22). The use of machine-assisted diagnosis by clinicians can increase their productivity (23). To minimise bias, cases are randomly reordered between rounds of assessment and a 4-week washout period is set between assessments to reduce recall effects. Diagnostic accuracy (measured as AUC) and clinician confidence (scored on a 5-point Likert scale) will be compared between rounds of assessment to quantify the impact of the model on decision consistency and clinician certainty. This multi-reader, multi-case framework ensures robust assessment of AI-human collaboration while addressing variations in real-world clinical work.

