## Introduction

1

Influenza causes 650,000 deaths annually and remains a threat to global health. Influenza has a mortality rate of approximately 20 per cent, and deaths due to influenza predominantly occur among infants, pregnant women, the elderly and the immunocompromised (1, 2). Although progress has been made with previously developed predictive tools and antiviral therapies, this has not reduced mortality from severe influenza (3). A key issue is the dynamic gap between clinical decision-making and risk of severe influenza. Evidence suggests that physicians are overconfident in the outcome of subjective clinical assessments leading to misdiagnosis and quality delays in severe influenza. Another factor, of course, arises from differences in the definition of ‘cure’ in the healthcare system (4, 5). A study by Valenzuela-Sánchez et al. (2024) reported that 34% of severe influenza cases were initially incorrectly classified as mild. The reason for this was an over-reliance on non-specific symptoms by clinicians when assessing influenza (6). This result implies that we need more objective and accurate tools to improve the accuracy of clinical judgement.

Artificial Intelligence (AI) can learn deeply from human health data so that closed-source predictive models can be constructed to identify high-risk patients. The current intersection of AI and healthcare data has shown revolutionary potential (7, 8). Yang et al. (2023) developed an influenza prognostic AI model using only city-scale data, which has achieved a performance AUC value of 0.89 (9). Of course, the lack of external validation of models constructed using AI across regions and healthcare resources means that more effort is needed for AI to address real-world clinical work (10). Dai et al. (2024) concluded that constructed AI diagnostic tools do not work well when put into prospective clinical practice due to population heterogeneity and data drift (11). This may be due to the lack of research-oriented personnel in the field of AI, leaving little understanding of dynamic risk prediction in high-risk subgroups in a clinical context (12).

The aim of our research is to develop and validate a deep learning-based diagnostic model for severe influenza. In order to be able to specify the research tasks at each stage, we established a methodological framework.

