#### Secondary outcomes

2.4.2

Secondary endpoints include diagnostic sensitivity and specificity, defined as the proportion of true severe influenza cases correctly identified by the model or clinicians, which reflects the tool’s capacity to minimize missed diagnoses in high-risk populations (30).

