#### Adjudication of ground truth

2.4.5

To ensure accurate outcome classification, an independent adjudication panel comprising three senior infectious disease specialists will retrospectively review all cases classified as severe influenza, verifying endpoints such as ICU admission, mechanical ventilation, or mortality. Discrepancies in outcome assessments among panel members will be resolved through majority vote, with detailed documentation of dissenting opinions. This rigorous process minimizes misclassification bias and enhances the reliability of outcome data, serving as the gold standard for model and clinician performance evaluation.

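### Phase III compares clinician confidence between rounds without regard to correctness, so a rise cannot be read as warranted or unwarranted certainty

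*Protocol article*

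**What the plan says.** Section 2.3.3 has each clinician read cases twice, first unaided and then with the model's risk score and contributing factors in view, with a four-week washout between rounds. Two measures are named for the contrast between rounds: "Diagnostic accuracy (measured as AUC) and clinician confidence". Of the latter it says that "clinician confidence (scored on a 5-point Likert scale) will be compared between rounds of assessment to quantify the impact of the model". The stated purpose in full is "to quantify the impact of the model on decision consistency and clinician certainty". The section presents the phase as a test of how model assistance affects the effectiveness of clinicians' decisions.

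The Introduction gives part of the reason for the study: "physicians are overconfident in the outcome of subjective clinical assessments leading to misdiagnosis and quality delays in severe influenza".

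Section 2.4.5 describes a panel-adjudicated outcome, "serving as the gold standard for model and clinician performance evaluation". Section 2.4.2 begins "Secondary endpoints include diagnostic sensitivity and specificity, defined as the proportion of true severe influenza cases correctly identified" and does not list confidence.

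**The concern.** Section 2.3.3 fixes the measure, the contrast and the purpose of the confidence comparison, but correctness of the diagnosis plays no part in it. A clinician who becomes surer of a right call and one who becomes surer of a wrong call move the result in the same direction. Elsewhere that might be a small matter of presentation. Here the Introduction treats misplaced certainty as one of the routes to missed severe influenza, so the two kinds of rise have opposite meanings for this study.

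What is at stake is how one of the two named Phase III measures can be read. If the model leads some clinicians to trust it when it is wrong, the planned comparison has no means of showing that.

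**Working it through.** **1. Is confidence linked to correctness anywhere?** The protocol states no figure to reproduce, so the first check is of the text.

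- Section 2.3.3: confidence compared between rounds, with no split by correctness.
- Sections 2.4.1 and 2.8.1 (primary outcome and its analysis): AUC only; reader confidence is not mentioned.
- Sections 2.4.2 and 2.8.2 (secondary outcomes and their analysis): sensitivity, specificity, predictive values and misdiagnosis rate; reader confidence is not mentioned.
- Section 2.4.5: a reference outcome is described but not applied to confidence.

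No section links the two.

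**2. What can a given mean rise conceal?** Let p be the share of correct diagnoses, assumed equal in both rounds.

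Mean rise = p × (rise on right) + (1 − p) × (rise on wrong)

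Fix the mean rise at 0.5 points. Both this figure and the values of p are assumptions.

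- p = 0.75: +0.5 on both; or 0.5/0.75 = +0.67 on right and 0 on wrong; or 0 on right and 0.5/0.25 = +2.0 on wrong.
- p = 0.66: the two extremes are 0.5/0.66 = +0.76 on right only, or 0.5/0.34 = +1.47 on wrong only.
- p = 0.85: the two extremes are 0.5/0.85 = +0.59 on right only, or 0.5/0.15 = +3.33 on wrong only.

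On a 1 to 5 scale the wrong-only extreme needs a starting mean on wrong diagnoses of at most 5 − 2.0 = 3.0 when p = 0.75, and at most 5 − 3.33 = 1.67 when p = 0.85. It therefore becomes implausible at high accuracy. The range between the extremes still gives the same mean rise.

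**3. What if accuracy improves as well?** Suppose errors fall from an assumed 30 per 100 readings to 21, the 30% reduction that the Introduction hypothesises as a minimum (30 × 0.70 = 21). Suppose further that half of the round 1 errors carry confidence 4–5.

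- Confidently wrong, round 1: 30 × 0.50 = 15.0 per 100.
- Break-even share of round 2 errors at 4–5: 0.50/0.70 = 71%. For starting shares of 30% and 60% it is 0.30/0.70 = 43% and 0.60/0.70 = 86%.
- At a round 2 share of 75%: 21 × 0.75 = 15.75 per 100, slightly more than in round 1.

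Mean confidence, with assumed group means:

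- Round 1: 0.70 × 3.6 + 0.30 × 3.2 = 3.48.
- Round 2, surer when wrong: 0.79 × 4.1 + 0.21 × 3.9 = 4.06, a rise of 0.58.
- Round 2, less sure when wrong: 0.79 × 4.1 + 0.21 × 2.9 = 3.85, a rise of 0.37.

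Under these inputs the overall comparison gives the larger rise to the less desirable pattern, although accuracy improves equally in both.

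**The case against.** A reader might infer that rising unwarranted confidence would be reported as a benefit of the model. The protocol does not support that. Section 2.3.3 speaks of impact, names no favourable direction and sets no success rule on confidence.

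A reader might also infer that the AUC comparison is blind to confident errors because confidence does not enter it. The article lists the two measures separately but never says which reader rating generates the ROC curve. A graded rating is usual input to a multi-reader ROC analysis. If the Likert score supplies it, confident errors would lower the AUC directly. Even then, an AUC does not say on which diagnoses confidence rose.

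The Introduction offers overconfidence as one factor among several. It attributes the cited 34% initial misclassification to reliance on non-specific symptoms. The passage also concerns unaided clinical judgement rather than model-assisted reading.

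Errors are counted elsewhere, through AUC between the same rounds and through sensitivity, specificity and the misdiagnosis rate. A rise in confidence with flat accuracy would therefore show in aggregate. In the third calculation total errors still fall by nine per 100, so Phase III would not have reached the opposite of the truth.

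Finally, modelling detail may sit in an analysis plan that is not shown. That weighs on severity. It does not remove the point, because the article itself fixes the contrast and its purpose, and as stated the contrast cannot serve that purpose alone.

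**Conclusion.** The concern holds in a limited form. As section 2.3.3 stands, a change in confidence between rounds cannot be interpreted on its own, because it does not separate certainty that is earned from certainty that is not. An AUC reported beside it does not locate the change.

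The size cannot be derived from the documents. The calculations use assumed accuracies, confidence levels and shares, and they show only that quite different patterns give the same or a misleadingly ordered mean rise. They are no forecast that confident errors will increase.

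This is a minor point. Confidence is not among the listed endpoints, the primary outcome does not depend on this comparison, and no trial conclusion is tied to it.

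**What to change.** In section 2.3.3:

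- Estimate the between-round change in confidence separately for correct and incorrect diagnoses, for example with an ordinal mixed model containing round, correctness and their interaction, with clinician and case as random effects.
- Judge correctness against the same reference outcome that is used for the AUC. This needs saying because section 2.4.5 describes panel review only of cases classified as severe.
- Report the rate of confidently wrong diagnoses (confidence 4–5 and wrong) per 100 readings in each round. Its denominator is all readings, so it is not disturbed when a reading changes from wrong to right between rounds.
- State which reader rating generates the ROC curve.

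No success rule on confidence is needed. The analysis uses each reading's diagnosis and confidence score together with the reference outcome that the AUC already requires, so no new data collection appears necessary. The cost is some wording, one additional model and one rate per round, and a confidence result that may look less favourable.

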#### Phase overview

2.1.4

The study comprises five sequential phases, which is based on the multiple nesting approach used in [name]’s past methods (16–20).

Model development: retrospective data (2019–2024) from 87 hospitals for training and internal validation.External validation-comparative study: benchmarking model performance against clinician diagnoses.Multi-reader, multi-case validation: assessing inter-physician variability with/without model assistance.Randomized controlled trial: evaluating real-time diagnostic accuracy in a clinician-AI collaborative setting.Prospective validation: real-world testing during the 2025 influenza season.

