#### Primary outcome

2.4.1

As the ultimate goal of this clinical trial is to create highly accurate AI models. Therefore the primary outcome metric was set as the area under the curve (AUC) (25). The AUC quantifies the discriminatory ability of the AI model so that it can distinguish patients who may develop severe influenza from those who will not. Since calculating the AUC requires the use of sensitivity, specificity, true positive rate, true negative rate, false positive rate, and false negative rate, more details describing these results can be found in our separate studies (16, 20).

To account for differences in diagnostic assessments after multiple clinicians read the cases, we planned to use the Dorfman-Berbaum-Metz (DBM) method. The DBM adjusts for differences in diagnostic assessments by clinicians so that AUC difference values between the two groups can be estimated (22). ROC curves were calculated using the pROC (version 1.18.0) software package (28). The AUC values as well as their 95% confidence intervals will then be calculated using MRMCaov (version 0.2.1) (27). For differences between the experimental and control groups, we expected to use the Mann-Whitney U test (29). Clinically significant improvement was defined as an AUC difference between the experimental and control groups greater than 0.15. The null hypothesis here is that the AUC difference is less than 0.7, and the AI model has no discriminatory power. Our method of using AUC to set thresholds not only follows statistical patterns, but is also highly compliant with the criteria for the development of AI-driven diagnostic tools.

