#### Primary outcome analysis

2.8.1

The AUC will serve as the primary metric to evaluate the diagnostic accuracy of the AI model. To account for variability inherent in multi-reader, multi-case study designs, the DBM method will be employed, which adjusts for differences in clinician interpretations and case complexity. Analyses will be conducted using the MRMCaov (v0.2.1) and pROC (v1.18.0) packages in R, generating AUC values with 95% confidence intervals (CIs) derived from non-parametric bootstrapping (1,000 iterations). A clinically significant improvement is predefined as a ΔAUC more than 0.15 between the model-assisted and control groups, with the null hypothesis assuming no discriminative capacity (AUC less than 0.70, equivalent to random guessing). This approach ensures robust statistical inference while addressing real-world diagnostic variability across clinicians and settings. Hyperparameter optimization was conducted via Bayesian optimization with 5-fold cross-validation, prioritizing AUC on the validation set.

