#### Secondary outcomes analysis

2.8.2

Secondary endpoints include diagnostic sensitivity and specificity, calculated using the Clopper-Pearson exact method for binomial proportions to determine the model’s and clinicians’ ability to correctly identify true positive and true negative cases, respectively. Differences between clinician and model performance will be assessed via the Mann–Whitney U test, a non-parametric method suitable for skewed distributions. Positive and negative predictive values (PPV/NPV) will be adjusted for influenza prevalence using Bayes’ theorem and reported with 95% confidence intervals to reflect their clinical utility in real-world settings. The misdiagnosis rate, defined as the sum of false positives and false negatives per 100 diagnoses, will be analyzed using an independent samples t-test (if normally distributed) or Wilcoxon rank-sum test (for non-normal data), quantifying the model’s impact on reducing diagnostic errors. These metrics collectively evaluate the model’s precision, reliability, and practical value in augmenting clinical decision-making.

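### Phase III says that comparing AUC and confidence between rounds quantifies decision consistency, but neither shows whether clinicians agree more with the model's help

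*Protocol article*

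**What the plan says.** Section 2.1.4 (Phase overview) describes the multi-reader, multi-case phase in one line, as "assessing inter-physician variability with/without model assistance". Section 2.3.3 opens more broadly: the two-round design is to evaluate how model assistance affects the effectiveness of clinicians' decisions. It then names two measures, diagnostic accuracy expressed as AUC and clinician confidence on a 5-point Likert scale. It states that these "will be compared between rounds of assessment to quantify the impact of the model on decision consistency and clinician certainty". On the design it says "All clinicians were required to undergo two rounds of tasks", with cases reordered and a 4-week washout between rounds.

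Section 2.4.1 says of the analysis method: "The DBM adjusts for differences in diagnostic assessments by clinicians so that AUC difference values between the two groups can be estimated". Section 2.8.1 describes the same method as one "which adjusts for differences in clinician interpretations and case complexity". The other endpoints in sections 2.4.2 and 2.8.2 are sensitivity, specificity, predictive values and the misdiagnosis rate. The only concordance measure in the article belongs to Phase V (section 2.3.5), where it compares the model with the adjudicated truth.

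**The concern.** Two measures are offered for two targets. Confidence matches certainty, which leaves AUC to stand for decision consistency. AUC compares each clinician's ratings with the adjudicated severe-influenza outcome and does not compare clinicians with one another. Two clinicians with the same AUC can be wrong on the same cases or on quite different ones.

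Read as written, an increase in AUC between rounds could be reported as evidence that the model makes clinicians more consistent, which it would not show. The distinction matters for a decision aid. A shared risk score can bring clinicians together on a wrong answer, or can raise accuracy without aligning them.

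**Working it through.** **1. Is any between-clinician measure named?**

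| Place | Quantity | What it compares |
|---|---|---|
| 2.3.3 | AUC | clinician with adjudicated outcome |
| 2.3.3 | 5-point confidence | clinician's own certainty |
| 2.4.1, 2.8.1 | DBM analysis of the AUC difference | reader differences, as an adjustment |
| 2.4.2, 2.8.2 | sensitivity, specificity, predictive values, misdiagnosis rate | diagnosis with adjudicated outcome |
| 2.3.5 (Phase V) | concordance | model with adjudicated outcome |

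No kappa, intraclass correlation, percent agreement or reader-variance outcome is named. The plan gives no agreement figure to reproduce.

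**2. Does AUC fix agreement?** This is an illustration.

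Inputs from the article: AUC 0.70 unassisted and 0.85 assisted (section 2.5.1). Assumed, because the article does not give them: 20% severe cases, all readers with the same true AUC, a common decision threshold, and the correlation *r* between readers' errors on the same case. AUC 0.80 is an assumed value between the two planning values.

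Model: the rating is normal with variance 1, with mean 0 in non-severe and *d* in severe cases, and the threshold is *d*/2.

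- *d* = √2 × Φ⁻¹(AUC)
- true-positive rate = Φ(*d*/2); false-positive rate = 1 − Φ(*d*/2)
- *p* = 0.2 × true-positive rate + 0.8 × false-positive rate (share called severe)
- *p*₁₁ = 0.2 × Φ₂(*d*/2, *d*/2; *r*) + 0.8 × Φ₂(−*d*/2, −*d*/2; *r*) (both of two readers call severe)
- observed agreement Po = 1 − 2*p* + 2*p*₁₁; chance agreement Pe = *p*² + (1 − *p*)²
- kappa = (Po − Pe)/(1 − Pe)

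At AUC 0.80: *d* = 1.414 × 0.8416 = 1.190. The true-positive rate is 0.724 and the false-positive rate 0.276. Then *p* = 0.2 × 0.7241 + 0.8 × 0.2759 = 0.3655, and Pe = 0.5362.

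- *r* = 0.1: *p*₁₁ = 0.1771, Po = 0.6232, kappa = 0.0870/0.4638 = 0.19
- *r* = 0.9: *p*₁₁ = 0.3056, Po = 0.8801, kappa = 0.3439/0.4638 = 0.74

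AUC does not contain *r*, so it is 0.80 in both. A simulation with 10 readers and 20,000 cases agrees with these kappas to about 0.01. With 30% severe the range is 0.22 to 0.75.

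**3. The same at the article's own AUCs (20% severe)**

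| AUC | kappa, *r* = 0.1 | *r* = 0.5 | *r* = 0.9 |
|---|---|---|---|
| 0.70 | 0.11 | 0.36 | 0.72 |
| 0.85 | 0.25 | 0.45 | 0.76 |

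If *r* fell from 0.5 to 0.1 while AUC rose from 0.70 to 0.85, kappa would fall from 0.36 (0.1759/0.4849) to 0.25 (0.1112/0.4482). Raw agreement Po would also fall, from 0.691 to 0.663, so the fall does not come from kappa's chance correction alone.

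**4. Thresholds.** In a simulation with 10 readers, 4,000 cases, 30% severe and *r* = 0.9, giving readers different cut-offs lowered mean pairwise kappa from 0.73 to 0.45 (AUC 0.70) and from 0.78 to 0.52 (AUC 0.85). AUC was unchanged, because it does not depend on the cut-off.

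**The case against.** The strongest reply is that inter-physician variability, in a multi-reader study, can mean how much readers differ in accuracy. Reader-specific AUCs and the DBM reader components bear on exactly that. This largely stands. In a simulation with 10 readers, AUC 0.80, about 20% severe and an assumed 348 cases, raising the error correlation from 0.1 to 0.9 moved the mean between-reader correlation of the DBM jackknife pseudovalues from 0.09 to 0.88. The observed between-reader standard deviation of AUC fell from 0.025 to 0.010. So the planned method does carry information on reader differences, and it would be wrong to infer that nothing in the analysis could separate these scenarios. But sections 2.4.1 and 2.8.1 use DBM to adjust the AUC comparison and name no reader component as an outcome. A spread of AUCs is also not agreement on individual cases.

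A reader might also infer that Phase III cannot answer its question at all. The article does not support that, because section 2.3.3 states a broader aim, the effectiveness of decision-making, which AUC and confidence do serve.

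Decision consistency is undefined and could mean a clinician's consistency with himself or herself across rounds. AUC and confidence do not measure that either, and section 2.1.4 speaks of differences between physicians.

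The choice of agreement coefficient can fairly be left to an analysis plan. The point here is different: the article names the measures and says what they quantify, and for consistency that statement is wrong.

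Finally, the fall in kappa in step 3 of the working shows what is possible and is not a forecast. A shared risk score would more plausibly raise the error correlation than lower it.

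**Conclusion.** The concern holds for the consistency and variability part of Phase III only. A between-round change in AUC or confidence does not show whether clinicians agree more. No between-clinician quantity is named as an outcome, although DBM output could describe variability in reader accuracy. The conclusion follows from what the measures are and does not depend on the illustration.

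The size does depend on assumptions: kappa from about 0.19 to 0.74 at a fixed AUC of 0.80, with 20% severe, equally accurate readers, a common threshold and error correlations from 0.1 to 0.9. Equal accuracy removes variability in reader accuracy by construction, so the figures speak only to case-level agreement.

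The primary AUC difference, Phase IV and the sample size are untouched. This should be corrected, but it does not threaten the trial's main result.

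**What to change.** In sections 2.3.3 and 2.8, do one of the following.

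1. Name as the Phase III consistency measure the change between the unassisted and assisted rounds in a multi-rater agreement statistic on the diagnosis (for example Fleiss' kappa). Compute it on cases read by more than one clinician, with an interval that accounts for the same readers and cases appearing in both rounds. Also report the between-reader spread of AUC per round from the DBM analysis, to describe variability in accuracy.
2. Otherwise, delete decision consistency (2.3.3) and inter-physician variability (2.1.4) as things that Phase III quantifies, and keep AUC for accuracy and the Likert score for certainty.

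Under option 1, splitting agreement by whether the model was right or wrong on the case is useful, because it separates real alignment from shared deference to a wrong score. It is not required.

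Option 1 costs a little extra analysis of readings already planned, provided that clinicians read overlapping cases. A multi-reader, multi-case design implies this, but section 2.3.3 does not state it outright and should. Option 2 costs only a wording change.
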